## DISCUSSION

3

Patients with CSP is often severely affected by the condition and many experiences depressive symptoms. These patients often pose a challenge as no apparent cause can be identified in 25–50% of the cases^5^, ^6^ which causes frustrations for both patients and clinicals. One study found that the average CSP patient will have seen an average of 4.5 urologist for the condition and have undergone 7.2 diagnostic interventions.^22^ Consequently, a thorough workup is necessary.

No efficient minimal invasive treatment is available, and in severe cases, patients are offered invasive treatments such as surgical denervation, orchiectomy, or epididymectomy.^8^ Therefore, BTX has been proposed as a new minimal invasive treatment, because BTX is used in the treatment of other pain syndromes. So far, only a few studies have examined the effect of BTX on patients with CSP with varying results. A pilot open‐label study reported significant pain relief in 72% of cases after 3 months with a reduction in effect after 3 months.^19^ A later randomized, double‐blinded, controlled trial showed no effect of BTX on scrotal pain after 1 month.^20^ In contrast to these two studies, we have chosen to refrain from lidocaine cord block prior to BTX injections as we do not want the analgetic effect of lidocaine to bias the effect of BTX.

Regular evaluation by questionnaires and physical examination after 4, 8, and 12 weeks has been chosen as BTX has shown to weaken muscles within 2 weeks^11^ and reduce neuropathic pain after 4 and 8 weeks.^23^ Hence, a close follow‐up seems appropriate.

The use of BTX as spermatic cord block is easy and minimally invasive and could offer patients long‐lasting pain relief. Long‐term treatment has shown efficacy and safety in patients with interstitial cystitis/bladder pain syndrome, which allows for retreatment if pain relief has been achieved.^24^ Only minor complications rated as CD‐1 by Clavien‐Dindo Classification^25^ such as local haematoma or infection are expected.

In conclusion, CSP has great bio‐psycho‐social consequences for many patients. Its complexity demands a thorough and standardized workup and treatment. We want to focus on the right treatment for the right patient by emphasizing the importance of a systematic approach when treating these patients. With this study, we want to show that BTX spermatic cord block might be an effective minimal treatment option for patients with CSP.

## PARTICIPANTS DISCONTINUATION AND WITHDRAWAL CRITERIA

4

All patients are free to discontinue their study participation at any time during the study for whatever reason without their decision affecting their future treatment and care. If possible, the reason for withdrawal should be reported to the study coordinator.

The investigator can exclude a patient from the study after inclusion based on the following:
Safety reasons (e.g., serious adverse event or another intercurrent illness); andPatient not willing to cooperate/non‐compliance.

The discontinuation should be documented and reported to the study coordinator. If a patient discontinues in the study, the subject number cannot be reused.

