Prior to BTX cord block, patients will answer the following questionnaires:
Visual analogue score for pain (VAS);Quality of life (EQ‐5D‐5L);Chronic Prostatitis Symptom Index (NIH‐CPSI);ICD‐10 depression questionnaire (MDI);Likert global assessment scale (L‐GAS); andInternational Index of Erectile Function questionnaire (IIEF).

For randomization, the research coordinator will place an information sheet containing the randomization in sealed envelopes (1:1 block randomization). At first treatment, the research coordinator will open a sealed envelope revealing the randomization and prepare the solution needed. The patient and physician will be blinded for the treatment.

In both groups, injection of either BTX or sterile saline will be given approximately 1–2 cm distal to the superficial inguinal ring near the spermatic cord using a gauge 23 needle. Before injecting the solution, the syringe is aspirated to exclude intravascular injection. The intervention arm will be given an injection of 50 IU BTX (Botox®, AbbVie A/S, Copenhagen) in a solution of 5 mL sterile saline both lateral and medial to the funicle for a total amount of 100 IU BTX mixed in 10 mL sterile saline. The control arm will receive two injections of a total of 10 mL sterile saline in the same manner. Both groups will be observed for 30 min after the injections. After 3 months at the end of the follow‐up, patients in the placebo arm will be offered BTX injections if wanted.

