### Sample size determination

2.2

Given that the true success rate for BTX, regarding the primary end point, is at least 0.70, the placebo success rate among controls is 0.20. We will need to study 23 experimental patients and 23 control patients to be able to reject the null hypothesis that the failure rates for experimental and control subjects are equal with probability (power) 0.9. The type‐I error probability associated with this test of this null hypothesis is 0.05. Considering potential dropouts, we will include 25 patients per group.

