### Safety

5.1

Based on former studies, BTX cord block has proven to be a safe minimal invasive procedure.^19^, ^20^ The studies found that the risk of complications is low. Unilateral transient hyperalgesia was reported, but no complications like bleeding or infection were registered. Events of adverse effects will be registered and treated until full resolution. Safety will be prospectively assessed and classified by Clavien‐Dindo Classification.^25^

An interim analysis will be conducted at 50% enrolment (*N* = 24 after loss to follow‐up, 12 patients per arm) accrual, and the decision to stop early will be governed by a significance level of 0.003. The decision to stop early will be guided both by interim results and clinical judgement, especially in the context of emerging, relevant literature.

Patients are covered by the Danish Patient Compensation.

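### Section 4 lets the investigator exclude randomised patients on treatment-related grounds without providing for continued follow-up, so week-12 outcomes can be lost for reasons linked to treatment

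*Protocol article*

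**What the plan says.** **Exclusion rule (section 4, Participants discontinuation and withdrawal criteria).** "The investigator can exclude a patient from the study after inclusion based on the following": safety reasons, with a serious adverse event or intercurrent illness as examples, and unwillingness to cooperate or non-compliance. The discontinuation is to be documented and reported, and the subject number is not reused. The section does not say whether outcomes are still collected afterwards.

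**Treatment and follow-up (sections 2.1 and 2.3).** Allocation is by "1:1 block randomization", with the envelope opened at first treatment. Treatment is one session of two injections. Questionnaires, including the VAS, are emailed at weeks 1, 2, 3, 4, 8 and 12. Examinations take place at weeks 4, 8 and 12.

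**Sample size (section 2.2).** "We will need to study 23 experimental patients and 23 control patients", and then "Considering potential dropouts, we will include 25 patients per group".

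**Interim analysis (section 5.1).** The interim sample is stated net of loss to follow-up, as 24 patients or "12 patients per arm".

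**Analysis (section 2.4).** Chi-squared tests are named for dichotomous variables. The article states no analysis population.

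**The concern.** In the blinded 12 weeks there is no second study treatment to withhold. Once the injections have been given, a patient can comply only with questionnaires and visits, and excluding that patient does little except stop outcome collection. Both listed grounds arise after treatment and can be affected by it. An adverse event may be caused by the injection, and a patient without relief may stop cooperating.

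If such losses differ between the arms, the patients still observed at week 12 are no longer the groups that were randomised. An analysis plan written later can define who is analysed, but it cannot recover a week-12 VAS that was never requested. The matter therefore belongs in section 4 and cannot be left to the analysis plan.

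**Working it through.** **1. Reproduce the sample size.** Inputs from section 2.2: "Given that the true success rate for BTX, regarding the primary end point, is at least 0.70" (p1 = 0.70), "the placebo success rate among controls is 0.20" (p0 = 0.20), power 0.90, and "The type‐I error probability associated with this test of this null hypothesis is 0.05". Sidedness is not stated; two-sided is taken.

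- Mean rate: (0.70 + 0.20)/2 = 0.45.
- Uncorrected: n = [1.960·√(2·0.45·0.55) + 1.282·√(0.70·0.30 + 0.20·0.80)]² / 0.50² = (1.379 + 0.780)² / 0.25 ≈ 18.6, so 19 per arm.
- With continuity correction: n' = (n/4)·[1 + √(1 + 4/(n·0.50))]² = (18.6/4)·(2.196)² ≈ 22.5, so **23 per arm**, as stated.
- Dropout allowance: 25 − 23 = 2 per arm, and 2/25 = 8%. Check: 23/(1 − 0.08) = 25.

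The sample size is not in error. The 23 are patients net of losses, as are the 24 at the interim.

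**2. Illustrate what arm-related removal does.** Assumptions: 25 per arm, no true effect, the same success rate p in both arms, exactly two failures removed from the BTX arm and none from placebo, uncorrected chi-squared at two-sided 0.05, all tables enumerated exactly. The bias is the expected BTX rate after removal minus p, that is 25p/23 − p.

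| Common success rate | Bias | Rejections favouring BTX, none removed | Two BTX failures removed |
|---|---|---|---|
| 0.20 (protocol's placebo rate) | 5/23 − 0.20 = +1.7 points | 2.7% | 3.9% |
| 0.40 (assumed) | 10/23 − 0.40 = +3.5 points | 3.0% | 5.6% |

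If two placebo failures are removed instead, the bias is −1.7 or −3.5 points, and rejections favouring BTX fall to 1.9% or 1.6%.

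**3. Dependence on the test.** Section 2.4 does not say whether the chi-squared test is continuity-corrected. With Fisher's exact test at the 40% rate, two-sided error goes from 3.0% to 4.5% when two BTX failures are removed, still below 5%. With uncorrected chi-squared it goes from 6.0% to 7.2%.

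**4. Cost of keeping everyone in the analysis.** Take 25 per arm as randomised and count a missing week-12 VAS as failure.

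- 2 lost per arm (the planned 8%): 0.70·0.92 = 0.644 against 0.20·0.92 = 0.184; Fisher power **0.901**.
- 4 lost per arm (16%, assumed): 0.588 against 0.168; Fisher power 0.836.
- 5 lost per arm (20%, assumed): 0.560 against 0.160; Fisher power 0.797.

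At the planned loss, the stated 90% power is kept with the planned 50 patients.

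**The case against.** **Leaving the study is not leaving the analysis.** A reader might infer from section 4 that excluded patients' data are discarded. It does not say so. It covers ending participation and documenting it, and an analysis plan not shown may define an all-randomised set. This stands, and limits the point to lost follow-up. It does not remove the point, because an analysis set cannot supply outcomes that were never collected.

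**The dropout allowance is conventional.** A reader might take the step from 23 to 25, and the interim count net of losses, as proof of a completers-only analysis. Both are consistent with that, but equally with an intention-to-treat analysis that allows for missing outcomes. They fix no analysis set. This stands.

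**The direction is not known.** Patient and physician are blinded, so exclusion for non-cooperation cannot knowingly favour an arm. Only minor complications are expected, so exclusions for serious adverse events should be few. Lack of relief is not a listed ground. At the design rates placebo would have 0.80·25 = 20 failures and BTX 0.30·25 = 7.5, so dropout among non-responders could well work against BTX. This stands: blinding prevents deliberate selection, but not losses caused by the treatment's own effects, in either direction.

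**The result is not generally fragile.** It is tempting to say that two or three exclusions would carry the p-value across 0.05. That is true only of borderline tables and depends on the test. At the design rates power with 25 per arm is 94.6% (Fisher) to 97.2% (uncorrected chi-squared), so the documents do not support it as a general statement.

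**Conclusion.** The point holds as a defect in a rule that the article itself fixes. Section 4 permits exclusion after randomisation on grounds that can depend on treatment and provides for no further outcome collection, although the emailed VAS could still be obtained.

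The documents do not establish that data are dropped, that bias will occur, or which arm it would favour. The illustrated shift of 1.7 to 3.5 points is modest and rests on three assumptions: exactly two removals, all of them BTX failures, and no true effect. The 40% rate is a further assumption. More removals, or more one-sided ones, would make it larger. The change is worth making because it needs only wording and lost outcomes cannot be recovered.

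**What to change.** Reword section 4 so that the investigator may stop study procedures for a randomised patient, but the patient stays in questionnaire follow-up to week 12 unless consent is withdrawn, and is analysed in the assigned arm. Record the reason and date of any discontinuation by arm.

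State a rule for a missing week-12 VAS. Counting it as failure is one workable choice for the responder outcome, supported by a sensitivity analysis that varies the assumed outcomes of missing patients separately by arm.

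**Cost.** Wording only, plus questionnaires that are already scheduled. Counting missing as failure is slightly conservative. No extra patients are needed at the planned loss of 2 per arm, but Fisher power falls below 0.90 if losses are heavier (0.836 at 4 per arm).

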## ETHICAL CONSIDERATIONS

5

The study will be conducted in compliance with the Declaration of Helsinki, Good Clinical Practice, and national laws and guidelines. The protocol was approved by The Regional Committees on Health Research Ethics for Southern Denmark before study initiation, and informed consent will be signed by all patients after thorough information has been given.

The use of BTX in pain treatment of CSP patients has been tested in small patient populations showing the treatment to be safe and not associated with severe side effects. The idea of using BTX in pain treatment is not new but well tested and documented for other medical conditions associated with other pain syndromes including bladder pain.^10^, ^11^, ^12^, ^13^, ^14^, ^15^ The value of BTX cord block is unsure, but BTX is widely used. Possible benefits of BTX are a significant reduction in pain evaluated by VAS and a more normal life.

Severe side effects observed when using BTX injections for other medical conditions are in general rare and treatable. When testing BTX injections in the two CSP studies, the complications observed, such as bleeding and local infections, can be considered minor, temporary, and treatable. Based on these data, we believe that it is responsible and safe to carry out the present study. We will only include patients that are thoroughly examined medically, patients where other medical reasons for the pain have been ruled out, and where the standard conservative treatment has shown no effect.

Patients will be informed about potential side effects, and every complication observed in the present study will be treated and followed closely. In addition, all complications will be registered in our database and reported.

The potential effect of our study is to improve treatment of pain in patients with CSP. Patients enrolled in the study will undergo both testing and minimal invasive surgery. This will be both time‐consuming and painful for the patients. However, at this point, the patient has been in pain for several months and there are no more conventional treatment options left, other than invasive surgery. In view of the potential benefits, the risk of minor complications such as infection and bleeding are to us acceptable.

We expect to observe a long‐lasting pain relief for up to 3 months in at least 70% of the patients in the intervention arm and in 20% of the patients in the placebo arm. We expect this to be sufficient to demonstrate the benefits of BTX injection for this group of patients. In addition, it will provide us with information about which patient group has the best effect of the treatment.

### Safety

5.1

Based on former studies, BTX cord block has proven to be a safe minimal invasive procedure.^19^, ^20^ The studies found that the risk of complications is low. Unilateral transient hyperalgesia was reported, but no complications like bleeding or infection were registered. Events of adverse effects will be registered and treated until full resolution. Safety will be prospectively assessed and classified by Clavien‐Dindo Classification.^25^

An interim analysis will be conducted at 50% enrolment (*N* = 24 after loss to follow‐up, 12 patients per arm) accrual, and the decision to stop early will be governed by a significance level of 0.003. The decision to stop early will be guided both by interim results and clinical judgement, especially in the context of emerging, relevant literature.

Patients are covered by the Danish Patient Compensation.

## DATA PROTECTION

6

Patient data are treated confidentially and will be stored according to the General Data Protection Regulation. No patient‐related information will appear in the analysis or published results. Signed consent forms and related paperwork will be uploaded in the database and saved in a locked cabinet. We expect to start inclusion in August 2024, and data will be deleted 10 years after this.

During the study, data from the patient's medical file will be registered in the database. Data include name, date of birth, CPR number, medical history related to the patients' CSP (date of first symptoms, symptoms, location of the pain, cause of the pain if known, results from physical examinations, description of scans of the scrotum, results from laboratory tests on blood and urine, and results from other medical tests), treatment (dates for treatment initiation and termination, medication given and dose, and effect of the individual treatments), results from questionnaires regarding pain and life quality, and effects and side effects related to the BTX or saline injection.

### Publications policies

6.1

It is the intention to report our research findings on a continuous basis in relevant national and international medical journals and present our data at appropriate conferences. Rules for authorship are as stated in “Uniform requirements for manuscripts submitted to biomedical journals” (http://www.icmje.org). In addition, the study is registered at http://clinicaltrials.gov/ with identifier NCT05112081 in accordance with guidelines.

Co‐authorships will follow the Vancouver Guidelines ICMJE | Recommendations | Defining the Role of Authors and Contributors.

The results will be analysed and published as soon as possible after sufficient inclusion and the 12 weeks follow‐up period. Any result (positive, inconclusive, or negative) will be published. Individual clinicians may not publish data concerning their patients that are directly relevant to questions posed by the study until the Trial Management Group has published its report. Studies using the present study data to evaluate end points other than those specified in this protocol can be published by participating physicians after approval from the Trial Management Group.

## Data Availability

The datasets used and/or analysed during the current study are available from the corresponding author on reasonable request.
